### Methods for additional analyses (e.g., subgroup analyses) {20b}

All planned analyses will be performed as described above.

### Methods in analysis to handle protocol non-adherence and any statistical methods to handle missing data {20c}

As is common in longitudinal studies, we anticipate attrition in data collection. We conservatively estimate that more than 80% of study participants will complete the 4-month survey, 80% will complete the 1-year survey and 60% the 2-year survey. These estimates are based on the BCW study [7] with further detail on retention provided below. In addition to the separate analyses described above, we will also fit a mixed effects logistic regression model that uses data from all post-treatment surveys. This model will allow us to estimate 1- and 2-year employment status while using all available data. Prior to fitting this model, we will evaluate any difference between participants with complete and incomplete data since mixed models provide unbiased estimates when data are missing at random (MAR) or missing completely at random (MCAR) but not when the missingness is nonignorable (NI) [64]. Multiple imputation and pattern mixture models will be implemented following guidelines and as appropriate to the data [64].

For all main analyses, participants will be analyzed in the arm in which they were initially randomized. However, it is possible that a subset of study participants in the arm randomized to receive the app will elect not to use it. Since we are collecting detailed tracking analytics for the app, we will describe its use and, in secondary analyses, evaluate whether app arm participants who use the app are different from app arm participants who do not use it in terms of baseline characteristics and the primary endpoint.

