### Criteria for discontinuing or modifying allocated interventions {11b}

Any patient who experiences significant study-related distress or asks to discontinue participation will be removed from the study.

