In BCW [7], approximately 50% of pre-diagnosis employed women who underwent chemotherapy were working 4 months after treatment completion. The difference in outcome between participants who did and did not have access to paid sick leave through their jobs was approximately 19% and was statistically significant (*p*=0.01). The mechanism of action of our intervention is hypothesized to be that working during the treatment period will provide job security to women and, therefore, lead to long-term job retention. Because paid sick leave provides similar job security, we will use a conservative effect size of 15% for our proposed intervention.

To identify an improvement of 15% in job retention 4 months post-treatment (i.e., 65% job-retention) in the arm randomized to receive the app, we would require 167 evaluable participants in each arm based on a 2-sided test with a 5% type I error and 80% power. We plan to recruit 420 women to obtain primary outcome data from 334 participants (assuming >80% retention 4 months post-treatment). *As noted above, we have estimated 80% retention 1 year post-treatment; we anticipate having higher retention 4 months post-treatment. Thus, we will have at least 80% power and 5% type I error to detect improvements in job-retention of 15% or more 1 year post-treatment. We expect further attrition by year 2. With a conservative 60% retention rate at 2 years, we will have 80% power to detect a difference of at least 17% for job retention at year 2. Using mixed models and important covariates, the detectable effect size for this comparison will likely decrease.*

*Sample size for sub-aim 1:* Characteristics of interest include chemotherapy regimen, symptom burden, race/ethnicity, language, and job tasks. We anticipate that, for example, 35% of participants in the study will have jobs that involve standing for long periods of time. This distribution will allow us to determine whether the association between the app and job retention varies by this job task.

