#### RCT participants

The research team will contact the treating physician (surgeon or medical oncologist, depending on who has most recently seen the patient in clinic) to verify that it is acceptable for the team to approach each patient about the study. If at the time of the initial medical oncology consultation no definitive decision is made regarding whether a potential participant will undergo chemotherapy, the research staff will communicate with the oncology provider regarding the final recommendation and patient decision regarding systemic therapy.

Research staff will approach participants at a post-operative visit with the surgeon, at their initial consultation with the medical oncologist, or a patient meeting or workshop (after obtaining permission from the meeting or workshop leader) to describe the study. Staff may also call patients about the study, and leave a voicemail, when applicable.

Our target study population is often hard to reach due to changes in phone number, loss of phone service, limited phone service, treatment side effects, lack of fixed working schedules, and change in address. In prior research, our team has experienced difficulties contacting members of our target population for an initial approach. However, after multiple attempts, we generally have success reaching our population. As a result, potential participants may be contacted at least 3 times. If the team is unable to contact the patient by phone, the team may approach the patient in clinic and offer the opportunity to learn more about the study. If the patient declines to participate by phone, no further attempts will be made to contact the patient.

If an individual is interested in the study, the research staff will assess their eligibility by going through the inclusion and exclusion criteria and asking the individual a set of screening questions. Answers will be recorded in the screening log and/or on the participants’ eligibility checklist. Patients approached who do not meet the eligibility criteria or decline participation will be asked about their self-efficacy to request accommodations at work and their answers will be recorded.

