#### On-treatment surveys

To limit participant burden, on-treatment surveys will be completed at approximately the mid-point of chemotherapy and with the last cycle only. Although the time between surveys will vary based on the regimen prescribed, the number of surveys administered to each participant will not vary. Participants whose chemotherapy regimen changes after treatment initiation will be surveyed at the projected mid-point of the regimen (on average 5–10 weeks). Such a change in adjuvant treatment regimen is rare and is not expected to affect study results. Moreover, detailed treatment information will be captured, and any effect of such a change will be evaluated in sensitivity analyses. These surveys will include an assessment of symptoms, accommodations, work status, and the two measures of self-efficacy (to ask an employer for accommodations and in patient-physician interactions).

Symptom control will be assessed using the NCI’s PRO-CTCAE®, which has been validated in English and Spanish [57, 58]. The scale may be used to measure symptoms over a period of anywhere between 1 day and 4 weeks [59]. Standard chemotherapy regimens for breast cancer have cycles varying in length from 1 to 3 weeks. Therefore, we will ask each patient to recall symptoms over the duration of the period since the last cycle of treatment. For example, if a patient is receiving chemotherapy on a 2-week cycle, her surveys will refer to her experience of symptoms over the course of the preceding 2 weeks. However, if she is receiving treatment on a 3-week cycle the questions will refer to the preceding 3 weeks.

Receipt of workplace accommodations will be assessed by asking participants about the kinds of accommodations they have requested, and whether these have been granted, including if the request was granted in full, in part, not at all, or if something else was offered in its place. Work will be measured in terms of employment status, work hours, and participant choice regarding these outcomes. Additional assessments will include self-efficacy to ask for accommodations and in patient-physician interactions.

Self-efficacy to ask for accommodations will be measured using a 5-item tool that we have developed and validated for this purpose (manuscript in preparation).

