Each of these specific risks is addressed below.Repercussions if an accommodation is requested and denied*Psychological repercussions*: Participants who request accommodations at work but are denied these may find that their self-efficacy to ask for accommodations decreases rather than increases as a result. A similar outcome could occur if their attempts to improve communication with the clinic team (e.g., a request for a more potent antiemetic or for a letter to take to the employer) are not well received. All research staff will be trained to identify signs of psychological discomfort in the participants. Any patient reporting significant distress (or indicating distress through other signs) will be referred to a licensed or board-certified mental health provider for additional evaluation, support, and/or referrals as needed.*Work-related repercussions:* Participants who report that they have experienced negative work-related repercussions of study participation will be referred to counseling and/or pro bono legal services, as appropriate and based on participant preferences. Moreover, we have incorporated an early stopping rule into the proposal, based on this potential adverse outcome. Additional details are included in the research plan and in the Data and Safety Monitoring Plan. In brief, we will monitor participants based on their answers to a survey question about whether their employer has treated them unfairly. Overall, approximately 6% of participants in the observational Breast Cancer and the Workforce study said they thought their employer had treated them unfairly. In the current study, we will call each participant who takes the 4-month survey and says her employer treated her unfairly. In the call, we will ask about the circumstances that led to this negative outcome. If there are 10 cases (per arm, at any time during the study) for whom the negative outcome is attributable to the app or booklet, we will stop the study. During the monitoring process, we will revise the intervention as needed.Failure to report a significant symptom to the clinic teamThe intervention that will be evaluated in this study includes information about common treatment-related symptoms. Additionally, patient reported symptoms will be assessed in participant surveys. The study team will not relay information about participants’ symptoms to the clinic team. Instead, participants will be expected to report any symptoms *directly* to their oncology providers. During the consent discussion participants will be informed that the information collected from them as part of the study is for research purposes only and will *not* be shared with the clinic team as part of their routine care. Furthermore, prior to initiating each survey participants will be reminded of the importance of communicating directly with the clinic team and relaying any information about symptoms directly to the appropriate physician or nurse. However, if a member of the research team or a nurse reviewer identifies an active and serious problem for a patient that should be addressed by a healthcare provider, he or she will notify the patient’s physician.Transitory distress related to thoughts about breast cancerThe risk of mild transitory distress prompted by the study intervention, control (informational brochure), usability testing, and surveys will be mitigated in several ways. First, all study materials will use clear and simple language and adhere with expert recommendations for surveys and interventions. Second, participants will be provided with contact information for the study investigators and the institutional review board at that subject’s recruitment site. All study staff who will interact with participants (i.e. in the consent process, through interviews, or when approaching participants due for surveys in clinic) will be trained in the protection of human subjects and will receive additional study-specific training to recognize and reduce participant distress. Any participant who feels distressed at any point will have the option to terminate study participation. We believe that the risk of distress due to study procedures in this in this study is low and if present, will be only mild and transitory. All research staff will be trained to identify signs of psychological discomfort in the participants. Any patient reporting significant distress (or indicating distress through other signs) will be referred to a licensed or board-certified mental health provider for additional evaluation, support, and/or referrals as needed.Breach of confidentialityAll data files will be password-protected and stored on secure servers in the Department of Psychiatry and Behavioral Sciences at Memorial Sloan Kettering Cancer Center. Access will be restricted to personnel working directly on this project. Files that must be shared with the rest of the study team or research coordinators will be shared using MSK’s secure file transfer system. Any printed data will be stored in a locked file cabinet and will be destroyed when no longer needed. Patient identifiers will be used to link information from multiple sources. We will assign patients a random number for data analysis. The matched list of patients and random study numbers will be kept by a member of the research team in a password-protected file. No attempt will be made to identify individual patients or providers beyond the use specified in this study. Publications and presentations of the data will adhere to all requirements for the protection of patient privacy and confidentiality, and no patient or provider will be individually identifiable. All data will be presented in aggregate form.

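### The distress-removal rule can create missing primary outcomes, the completer comparison cannot detect nonignorable loss, and the stated analyses leave on-treatment work status unused

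*Protocol article*

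**What the plan says.** All references are to the Protocol article.

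- **Removal.** Section {11b}: "Any patient who experiences significant study-related distress or asks to discontinue participation will be removed from the study". The harms section {22} says instead that a participant who feels distressed "will have the option to terminate study participation", and provides a mental-health referral for significant distress. Section {20c} keeps participants in their randomised arm for all main analyses.
- **Check on missingness.** Section {20c}: "we will evaluate any difference between participants with complete and incomplete data since mixed models provide unbiased estimates when data are missing at random" or MCAR, but not when missingness is nonignorable.
- **Models.** The powered analysis is a direct two-arm comparison at 4 months (section {20a}). Section {20c} adds a plan to "fit a mixed effects logistic regression model that uses data from all post-treatment surveys", aimed at employment status at 1 and 2 years. The same section then names multiple imputation and pattern mixture models, to be used according to guidelines and where the data make them suitable.
- **Data on file.** At the mid-point and last cycle of chemotherapy, "These surveys will include an assessment of symptoms, accommodations, work status, and the two measures of self-efficacy".
- **Retrieval.** The section on RCT surveys and measures provides for calls, email or a postcard to non-responders to establish employment status.

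**The concern.** Three stated rules pull against an unbiased as-randomised comparison.

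First, {11b} takes a distressed woman out of the study, not only off the app or booklet. Section {22} lists psychological and work-related repercussions of a denied accommodation request among the study's risks. Requesting accommodations is what the intervention promotes, and a denial may go with losing the job. Removal on this ground may therefore depend on both arm and outcome, and an as-randomised rule cannot recover an outcome that was never collected.

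Second, a comparison of complete and incomplete participants is given as the ground for trusting the mixed model. If it shows little difference, a reader may conclude that the model is safe and that methods for nonignorable loss are not needed. The comparison cannot support that conclusion.

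Third, a woman who reports work status twice during chemotherapy and then completes no post-treatment survey contributes nothing to the primary comparison or to the mixed model. Yet the protocol's own rationale for the effect size is that working through treatment leads to keeping the job, so this status should be a strong predictor of her outcome.

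At stake is the primary contrast, with about 20% loss planned at 4 months against a 15-point target.

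**Working it through.** **1. The plan's own figures.** The design assumption is that "approximately 50% of pre-diagnosis employed women who underwent chemotherapy were working 4 months after treatment completion", with 65% targeted in the app arm; "we would require 167 evaluable participants in each arm based on a 2-sided test with a 5% type I error and 80% power". The unpooled normal approximation gives

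n = (1.960 + 0.842)² × (0.50×0.50 + 0.65×0.35) / 0.15² = 7.849 × 0.4775 / 0.0225 = 166.6, so 167 per arm.

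Recruitment: 334 / 0.80 = 417.5, so 418 against 420 planned. No stated figure is wrong on this point. Planned loss is 20% at 4 months and 40% at 2 years, where the stated detectable difference is 17 points.

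**2. What the completer comparison can show.** MCAR implies that completers and non-completers do not differ systematically on observed variables, so a difference argues against MCAR. MAR and nonignorable loss differ only in whether, given what was observed, response still depends on the unobserved outcome. No comparison of observed variables can test that.

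**3. Illustration of size (assumed inputs).** The documents give no response rates by work status. Let p be true retention, and let w and u be the response rates in working and non-working women. Responders then show

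p·w / [p·w + (1−p)·u].

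Take p = 0.50 in both arms (no effect):
- App arm, w = 0.90, u = 0.70: response 0.45 + 0.35 = 0.80; observed 0.45 / 0.80 = 0.5625.
- Booklet arm, w = u = 0.80: response 0.80; observed 0.40 / 0.80 = 0.500.
- Spurious difference: 6.25 points, with identical response rates in the two arms.

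With 168 responders per arm, SE = √[(0.5625×0.4375 + 0.25)/168] = 0.0543 and 0.0625/0.0543 = 1.15. A two-sided 5% test would then reject in about 21% of trials.

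With 90%/70% in **both** arms, each shows 0.5625 and the bias is zero. If the true rates were 50% and 65%, the same pattern in both arms would give 0.585/0.830 − 0.5625 = 0.705 − 0.5625 = 14.2 points, a slight attenuation.

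**4. A range of other assumptions.** With loss m and true retention q among the lost, responders show (p − m·q)/(1 − m). With 210 per arm and p = 0.50 in both:

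| Loss, booklet/app | Retention among lost, booklet/app | Bias (points) | Rejection rate |
|---|---|---|---|
| 20%/20% | 30%/30% | 0 | 5% |
| 18%/22% | 30%/30% | +1.3 | about 5.6% |
| 15%/25% | 30%/30% | +3.1 | about 9% |
| 20%/20% | 50%/30% | +5.0 | about 15% |
| 20%/20% | 60%/30% | +7.5 | about 28% |

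**5. Sensitivity of an on-target result.** Suppose completers show 50% and 65% (168 per arm, 42 lost per arm) and 50% of the lost booklet women kept their jobs. The calculation treats filled-in outcomes as observed, so it is only indicative.
- 40% of lost app women working: (109.2 + 16.8)/210 = 0.60; difference 0.10; z = 2.07.
- 30% working: (109.2 + 12.6)/210 = 0.58; difference 0.08; z = 1.65, no longer significant.
- All missing counted as not working in both arms: 0.65×0.8 − 0.50×0.8 = 0.52 − 0.40 = 12 points.

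**The case against.** The strongest reply is that section {20c} does not stop at the completer comparison. It names multiple imputation and pattern mixture models, and the latter are a standard approach to nonignorable loss. Imputation variables and sensitivity scenarios are commonly left to an analysis plan, and none is shown here. This stands, and it rules out two stronger readings. A reader might infer that the plan has no answer to informative loss, but the named methods are an answer, though a conditional one. A reader might also infer that on-treatment work status is ignored altogether. That is shown only for the primary comparison and the mixed model, because the imputation variables are not stated.

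The protocol also retrieves employment status actively from non-responders, which should reduce loss. It does not say whether removed women are included. Equally, {11b} does not say that outcome collection ends for them, so the lost outcomes follow from a literal reading and are not stated. Section {22} expects distress to be low, mild and transitory, so few women may be affected.

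It is tempting to argue that job loss itself makes these women unreachable, citing the description of the population as "hard to reach due to changes in phone number, loss of phone service". That text concerns the first recruitment approach, and it adds that contact generally succeeds after repeated attempts. It is not evidence about follow-up.

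Finally, the bias figures need loss that differs between arms in amount or in its relation to work status, and no passage supplies such a pattern.

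**Conclusion.** The point holds in limited form and should be acted on. Sections {11b} and {22} conflict, and {11b} sits badly with the as-randomised rule in {20c}. The completer comparison cannot do what it is used for. The primary comparison and the mixed model leave out work status that the trial already collects. Multiple imputation and pattern mixture models are named, but their use is conditional and follows a check that cannot detect nonignorable loss.

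The documents do not establish that the result will be biased, in which direction, or by how much. Under the assumed patterns above, the spurious difference with no true effect runs from 0 to 7.5 points against a 15-point target. It is zero when loss and its relation to work status are the same in both arms.

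**What to change.** 1. Reconcile {11b} with {22} and with the as-randomised rule in {20c}. State that stopping the app or booklet does not end collection of employment status unless the woman withdraws consent for follow-up, and that the retrieval contacts apply to her.
2. For the 4-month endpoint, specify multiple imputation by arm, using baseline variables and work status at the mid-point and end of chemotherapy.
3. Keep the completer comparison as a description of who is missing. Run the pattern-mixture sensitivity analysis whatever it shows: delta-adjusted by arm, including missing counted as not working.

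The cost is protocol wording, modest extra analysis, and some continued contact with women who have stopped the intervention. No new instrument is needed, since employment and on-treatment work status are already in the surveys.

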### Plans to give access to the full protocol, participant level-data and statistical code {31c}

In accordance with the NIH Policy on Dissemination of NIH-funded Clinical Trial Information, this study is registered with ClinicalTrials.gov, and results information will be submitted no later than 1 year after the trial's primary completion date. Sharing of study data and the statistical code will be handled on a case-by-case basis.

